### Participant recruitment

Participants will be recruited from the inpatient rehabilitation unit of an acute hospital (i.e. SGH) and an inpatient rehabilitation hospital (i.e. AMKTHKH). Each site is expected to recruit approximately 50 participants (25 intervention and 25 controls).

### Screening process

Recruitment will be initiated while the stroke patient is still in the hospital. The research assistant will first screen the medical records for current admissions and medical histories including the list of diseases and conditions at the hospital sites. Once potential patients are identified, the research assistant will approach them and provide information about the study, both in written and verbal form, only after they have indicated their interests. The research assistant has to review the inclusion and exclusion criteria of patients that cannot be determined through medical records.

### Informed consent and enrollment

After eligibility is confirmed, details of study will be explained to potential participant. Once participant agrees to participate, Informed consent is obtained, patient is enrolled and randomization only occurs after enrollment.

### Baseline assessments

The data collected from all participants at baseline are detailed in Table 1. Baseline data collection will be conducted by research assistants who have been trained in administering the questionnaire and assessment tools by the study coordinator. As this study is a single blind (evaluator-blind) randomised controlled trial, research assistants who are involved in the recruitment of participants are not allowed to be involved in the assessment of participants at 3 months and 6 months.

**Table 1 Tab1:** Baseline assessments

**Personal Information**	**Admission information**	**History of current stroke**
Date of birth	Ward Class	Date of stroke onset
Ethnicity	Date of admission	Type of stroke
Gender	Date of discharge	First or recurrent stroke
Marital Status		Stroke characteristics
		-Side of hemiparesis
		Left
		Right
		-Stroke type
		Infarct
		Bleed
		Both
		Undefined
		-Stroke severity (according to Modified Ranking Scale)
**Co-existing conditions**	**Caregiver**	**Additional tests**
Cardiovascular disease	Spouse	Depression according to Center for Epidemiologic Studies – Depression Scale (CESD-11)
Hypertension	Child	
Peripheral vascular disease	Maid	
Chronic obstructive pulmonary disease	Others	Cognitive function according to Mini-Mental State Exam (MMSE)
Arthritis or other musculoskeletal condition	None	Euro-QOL (EQ-5D)
Diabetes		

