**Methods/design:**

This is a single blind (evaluator blinded), parallel, two-arm randomised controlled trial study design involving 100 recent stroke patients. The inclusion criteria are age ≥40 years, having caregiver support and recent stroke defined as stroke diagnosis within 4 weeks. Consenting participants will be randomized with varying block size of 4 or 6 assuming a 1:1 treatment allocation with the participating centre as the stratification factor. The baseline assessment will be done within 4 weeks of stroke onset, followed by follow-up assessments at 3 and 6 months. The tele-rehabilitation intervention lasts for 3 months and includes exercise 5-days-a-week using an iPad-based system that allows recording of daily exercise with video and sensor data and weekly video-conferencing with tele-therapists after data review. Those allocated to the control group will receive usual care. The primary outcome measure is improvement in life task’s social activity participation at three months as measured by the disability component of the Jette Late Life Functional and Disability Instrument (LLFDI). Secondary outcome variables consist of gait speed (Timed 5-Meter Walk Test) and endurance (Two-Minute Walk test), performance of basic activities of daily living (Shah-modified Barthel Index), balance confidence (Activities-Specific Balance Confidence Scale), patient self-reported health-related quality-of-life [Euro-QOL (EQ-5D)], health service utilization (Singapore Stroke Study Health Service Utilization Form) and caregiver reported stress (Zarit Caregiver Burden Inventory).

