### Quality of life

We will use the Euro-QOL (EQ-5D) to measure patients’ quality of life. The EQ-5D is a standardized health-related quality of life questionnaire applicable to a wide range of health conditions and treatments, and it provides a simple descriptive profile and a single index value for health status which can be used in the clinical and economic evaluation of health care [27]. It is designed for self-completion by respondents. It consists of 16-items which measure health state on five dimensions: mobility, self-care, usual activities, pain/discomfort, and anxiety/depression. Each dimension comprises of three levels with their score: no problem = 1, some problem = 2, extreme problem = 3. The result is represented in a 5-digit number, in which each digit shows the level of the respective dimension [27]. Participants will also be asked about their health status and to indicate a value between 0 to 100 where 0 represents the worst health imagined and 100 represented the best health imagined [27]. The EQ-5D will also be administered at baseline for both intervention and control groups in order to calculate change in health-related quality of life before and after the trial which is needed for cost-effectiveness analysis.

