### Research data management and security

All patient information to and from the server will be encrypted via Hypertext Transfer Protocol Secure (HTTPS) which ensures no external parties are able to view it during transfer, a protocol similar to those used by online banking systems. Data access from server is also authenticated by a passphrase which is supplied from the therapist application, ensuring only the patient’s therapist will be able to request and review patient data. Regarding security on the server side, we will be using the Apache server running on a Unix-based operating system and have taken recommended measures to minimise vulnerabilities from hacking.

Only an administrator (in this study, this is the Study Coordinator) will be able to view all patients (both groups) and therapists (intervention group only) data, and update the system in an event of data entry error. The administrator will have privileges to add patients & therapists to the database, pair patients to therapists as well as to update and view all patient data. The independent assessor (blinded evaluator) will be able to input outcome data into the system for both groups at 3 month and 6 month. However, independent assessor will not have access to any participant information other than the latter’s initials and unique study number. The biostatistician will only have read-only access to all the patients’ data for research purposes. However, the biostatistician will not be able to manipulate or distort the data. The biostatistician can also download data for research purposes in the form of an Excel file. All these measures have been put in place to ensure that there is no leakage of patients’ information and only authorized individuals have full access to the secured data.

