### Statistical analysis

#### Sample size

Chumbler et al’s paper had similar tele-rehabilitation intervention at 0, 3 and 6 months, and the same primary outcome measure, the Difficulty dimension of the Disability component of the Jette LLFDI [12]. Even though the mean score derived from the results in Chumbler et al’s paper was 11 [12], a mean score of 8 was used in this study due to different geographical and socio-cultural context; Chumbler et al’s study was done in the United States whereas this study was done in Singapore, where rehabilitation is less well-accepted. Hence, based on a two-sided test of 5 % and a power of 90 %, and assuming a difference in mean scores of 8 and a standard deviation of 16, and a correlation of 0.6, a total sample size of around 86 (intervention = 43, controls = 43) was calculated to be adequate. Accounting for 14 % attrition rate, the minimum sample size was determined to be 100 (intervention = 50, controls = 50). It is planned that 100 participants will be recruited within 2 years, after which an additional 6 months is needed for follow-up.

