#### Analysis for outcome measures

Data entered will be checked for accuracy at least twice by at least two independent assessors. To understand the structure of missing data and to reduce bias from uncertainty of missing data, multiple imputations will be performed using the Markov Chain Monte Carlo method. All scale-based measures used in this study will be screened via an internal consistency test (Cronbach’s alpha test) before creating a summative score. Furthermore, rigorous validity tests will be performed in two ways: person-centered tests (latent class analysis) and variable-centered tests (exploratory and confirmatory factor analyses).

For descriptive statistics, independent two-sample *t*-test and Analysis of Covariance (ANCOVA) will be performed on all continuous outcome measures (i.e. Shah-modified BI, ABC Scale, gait speed, two-minute walk test and ZBI) between tele-rehabilitation vs. usual care group if outcomes are normally distributed. Mann–Whitney *U* test will be performed on data with skewed distribution to test differences between treatment groups. Chi-square test will be performed on categorical variables. Confounders are age, gender, ethnicity and marital status. Multiple linear regressions will be used to adjust for differences in confounders between intervention and control groups for continuous outcome variables. Ordered logistic regressions will be used to adjust for differences between intervention and control groups for continuous categorical variables. For these multivariate linear and logistic regressions, we will use survey analysis processes with robust standard errors which accounts for nesting effects within patient data as a result of clustering by different recruitment centers. For all statistical analyses, the level of significance (α) will be taken at 0.05. Analyses will be based on the intention-to-treat approach. We will use STATA version 12 for statistical analysis and significance level is set at P < 0.05.

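### The primary outcome is an improvement in LLFDI, but the baseline table omits the LLFDI, the 0.6 correlation is undefined, and adjustment leaves out stroke severity and handles site weakly

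*Protocol article*

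**What the plan says.** - **Primary outcome.** Abstract, Methods/design: "The primary outcome measure is improvement in life task’s social activity participation at three months", measured by the disability component of the LLFDI.
- **Baseline data.** Baseline assessments: "The data collected from all participants at baseline are detailed in Table 1". Table 1 is detailed, down to ward class and marital status. Its additional tests are CESD-11, MMSE and EQ-5D, and stroke severity is recorded on the modified Rankin scale. The LLFDI is not listed.
- **Baseline outcome measure.** Quality of life: "The EQ-5D will also be administered at baseline for both intervention and control groups in order to calculate change in health-related quality of life". No other outcome section says this of its instrument.
- **Sample size.** The calculation is "based on a two-sided test of 5 % and a power of 90" per cent, with a difference of 8, SD 16 and a correlation of 0.6, giving 43 per arm. The text does not say which two measurements the 0.6 relates.
- **Adjustment.** Analysis for outcome measures: "Confounders are age, gender, ethnicity and marital status". The regressions use robust standard errors for clustering by recruitment centre. Under Randomisation method, site is the stratification factor, and there are two sites.

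**The concern.** An improvement needs a starting value. If the LLFDI is first measured at three months, the planned primary quantity cannot be formed for any participant, and the most useful covariate for the three-month score is lost. A measure missed before randomisation cannot be recovered later. A baseline-to-follow-up reading of the 0.6 would then credit the sample size with a precision gain that the data cannot deliver.

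The covariate list is a second, independent weakness. Stroke severity is collected and is likely to predict later participation better than marital status does, yet it is not used. Site was used to stratify, so the analysis would normally carry it as a covariate.

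**Working it through.** **1. The texts side by side.** The endpoint wording requires baseline LLFDI. The section that claims to detail the baseline data does not list it. The only outcome instrument said to be given at baseline, EQ-5D, is also the only one of the listed outcome instruments in Table 1. Those two places agree with each other and conflict with the endpoint.

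**2. The plan's own figure.** Inputs from the Sample size section: two-sided 5%, power 90%, difference 8, SD 16.

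Per arm, n = 2 × 16² × (1.960 + 1.282)² / 8² × f = 84.06 × f, where f depends on how a correlation of 0.6 is used:

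| Reading of 0.6 | f | n per arm |
|---|---|---|
| Not used, three-month score only | 1 | 85 |
| Change from baseline | 2(1 − 0.6) = 0.8 | 68 |
| ANCOVA on baseline | 1 − 0.6² = 0.64 | 54 |
| Mean of three- and six-month scores | (1 + 0.6)/2 = 0.8 | 68 |

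None of these gives 43. The one-sample formula, 84.06 / 2 = 42.03, rounds up to 43, but it drops the two-arm factor and does not use the 0.6. The attrition step does reproduce: 86 / (1 − 0.14) = 100.

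**3. What a baseline LLFDI is worth at 43 per arm.** ANCOVA reduces the SD to 16 × √(1 − ρ²), where ρ is the baseline to three-month correlation. The noncentrality is 8 / (SD × √(2/43)). Power is from the noncentral t with 84 degrees of freedom. The documents give no ρ known to be baseline to three months, so 0.3 to 0.6 is an assumed range.

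| ρ | Residual SD | Noncentrality | Power |
|---|---|---|---|
| No baseline | 16.00 | 2.318 | 63.0% |
| 0.3 | 15.26 | 2.430 | 67.1% |
| 0.4 | 14.66 | 2.530 | 70.6% |
| 0.5 | 13.86 | 2.677 | 75.4% |
| 0.6 | 12.80 | 2.898 | 81.7% |

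The normal approximation is about one point higher (64.0% with no baseline, 82.6% at 0.6). A simple change score at ρ = 0.6 has SD 16 × √0.8 = 14.31 and power 72.7%. At ρ = 0.5 its variance factor is 2(1 − 0.5) = 1, so it gains nothing over the three-month score, and below 0.5 it loses power. This is why ANCOVA is preferable to change.

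**4. Chance imbalance.** If the baseline SD is also 16 (an assumption), the standard error of a chance baseline difference between arms is 16 × √(2/43) = 3.45 points, against a target effect of 8.

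**5. Site.** Robust standard errors clustered on two centres rest on 2 − 1 = 1 degree of freedom between clusters. The variance estimate needs many clusters to be trustworthy. A fixed effect for site reflects the stratified design without that difficulty.

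**The case against.** The strongest reply is that Table 1 may simply be incomplete in a condensed article. The Sample size section likens the design to a study with assessments at 0, 3 and 6 months and the same outcome. Web-based data entry has research assistants entering baseline and outcome data. The Standardization section trains them in the outcome measures, and ANCOVA is planned. This keeps open the possibility that the LLFDI is in fact collected at baseline. None of it says so, however, and the ANCOVA sentence names no baseline value as covariate. If the LLFDI is collected, Table 1 is wrong and still needs correcting.

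The EQ-5D sentence gives its own reason, the cost-effectiveness analysis, so it is supporting evidence and not proof. The statement that the independent assessor "will be able to input outcome data into the system for both groups at 3 month and 6 month" describes the blinded assessor's access rights and shows nothing about baseline, so I place no weight on it.

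A three-month comparison between randomised arms is unbiased without any baseline score. Some correction for starting function is also possible from baseline modified Rankin score and EQ-5D. Both points stand: what is lost is precision and the stated endpoint, not validity.

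A reader might go further in four ways that the article does not support:

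- **Site is ignored.** It is the stratification factor and enters through the clustered standard errors. The criticism is of how it is handled.
- **The covariate list prevents change from being computed.** Covariates have no bearing on that. Only the missing baseline LLFDI does.
- **The 0.6 is unusable.** It is undefined. A three- to six-month correlation could serve a repeated-measures analysis, although that reading needs 68 per arm and does not explain 43.
- **Ethnicity and marital status must be dropped.** That is a preference, and nothing in the document requires it.

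**Conclusion.** The point holds. The stated primary endpoint and the stated baseline data set contradict each other. Followed as written, neither LLFDI change nor ANCOVA on baseline LLFDI is possible. The 0.6 has no stated referent and, if it means baseline to three months, no baseline to support it.

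At 43 evaluable per arm, with difference 8 and SD 16, power is 63% without a baseline and about 67% to 82% with one, for ρ from 0.3 to 0.6. The upper figure holds only if 0.6 is the baseline to three-month correlation. A reader might infer that adding the baseline restores the planned 90%. It does not: even at 0.6, ANCOVA needs 54 per arm. That shortfall is a separate sample-size problem.

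The omission of stroke severity and the two-cluster standard errors are a lesser, separate weakness. The LLFDI gap is the part that must be settled, because it cannot be repaired after randomisation.

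**What to change.** 1. State whether the LLFDI disability component is measured at baseline. If it is, correct Table 1. If it is not, add it to the baseline assessment, which Randomisation method already places before randomisation.
2. Make the primary analysis an ANCOVA of the three-month LLFDI score on baseline LLFDI, with site as a fixed effect and baseline modified Rankin score as a covariate. Replace the centre-clustered standard errors with this site term.
3. State which two measurements the 0.6 relates and where it comes from.

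**Cost.** One more questionnaire at an existing visit, by assistants who are already trained in the outcome measures. Inpatients' LLFDI may correlate less than 0.6 with the three-month score, in which case the gain is at the lower end of the range above. The site and severity terms need no new data. The Usual care section indicates that the trial was already under way, so a new baseline measure helps only participants not yet randomised. For the others, modified Rankin score and EQ-5D are the baseline function measures at hand.

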#### Depression according to Center for Epidemiologic Studies – Depression Scale (CESD-11)

Informal caregivers will rate each item/symptom on the 11-item Centre for Epidemiologic Studies Depression (CES-D) scale as occurring none/rarely (score = 0), sometimes (score = 1) or often (score = 2) during the past week. Items scores will be summed to obtain a CES-D score (range: 0–18). A previous study from Singapore has reported that the 11-item CES-D has good internal consistency (Cronbach’s alpha = 0.76) and its factor structure matched with that reported in the original validation of the scale. In sensitivity analysis, the CES-D score, a continuous variable, is considered as the outcome.

#### Cognitive function according to Mini-Mental State Exam (MMSE)

The Mini-Mental State Examination (MMSE) is the most commonly used screening tool for cognitive impairment and dementia worldwide. A number of studies have examined the accuracy of the MMSE in the detection of dementia. In Singapore, the localised MMSE version discriminated well between elderly with and without dementia (cut-off 23/24, sensitivity 97.5 %, specificity 75.6 %) [17].

### Standardization

Research assistants and tele-therapists will receive training provided by the study coordinator. The research assistants will be trained in assessing the eligibility of potential participants, obtaining informed consent from participants, randomization process, STARS tele-rehabilitation intervention protocol, the use of tele-rehabilitation system from the patient user interface, patient education on the use of the tele-rehabilitation system (including provision of written instructions to the participant), obtaining outcome measures for both intervention and control groups and documenting the measures. On the other hand, the tele-therapists will be trained in the use of tele-rehabilitation system from the tele-therapist user interface, progression protocols and documenting patients’ progress.

Competency of the tele-therapists and research assistants in their respective responsibilities will be assessed by the study coordinator at the end of the training programme. 90 % competency prior to participating in the study must be attained. To avoid drift, maintenance of competency is important in a multi-site clinical trial. Re-assessment will be done by the study coordinator every 6 months during the study at both sites.

### Randomisation method

Randomization will be conducted after baseline assessment. The participants will be randomized into one of the two groups: tele-rehabilitation intervention and usual care based on equal allocation with randomly varying block sizes of four and six. As the study is conducted in two sites, stratified randomisation will be carried out assuming study site as the stratification factor. The randomisation list is generated using the ***ralloc*** package of Stata 11 (StataCorp LP, College Station, TX, USA).

### Intervention

The tele-rehabilitation intervention has three components: (a) the hardware, (b) the software and (c) the progressive rehabilitative exercises. Prior to the tele-rehabilitation intervention, the research assistant, who previously recruited the participant, will train the participant and their caregiver on the usage of the devices and sensors. The participant and their caregiver will learn how to wear the sensors, operate the hardware and perform all the rehabilitation exercises with the hardware. The training is usually done within 1–3 sessions, with each session being an hour long, until the participant and caregiver are competent in its use. These sessions are done before the discharge of participant and, if necessary, in their homes after discharge. To ensure that the participant/caregiver is able to use the devices and sensors, the participant/caregiver must pass a competency check list, such as switching on the iPad and applying the sensors. Additionally, a baseline visit is scheduled for set-up of tele-rehabilitation system in the participant’s house.

#### Hardware component

The hardware component comprises of an iPad, two limb sensors, a heart rate and blood pressure monitoring set and chargers for these devices. A stable movable floor-mounted flexible iPad stand will be provided to allow easy positioning of iPad to video-record exercises performed by the patient. Engineering details on the tele-rehabilitation system infrastructure and the accuracy of the sensors have been published [18, 19]. Only basic details necessary to understand how the tele-rehabilitation system works are mentioned here.

The limb sensor node is used in the system to determine the orientation of the limb being exercised, which is in turn sent to iPad to determine the number of repetitions and range of motion. Each sensor node consists of an ATMEGA328 microprocessor embedded on a printed circuit Board with three motion sensors and attached to a Bluetooth module. The three motion sensors attached are: ITG3200 (gyroscope) and LSM303DLHC (accelerometer and magnetometer). The Bluetooth module, which is a BLE112-A low energy single mode module produced by Bluegiga tech, is required for wireless communication with iPad.

The data collected from these motion sensors are polled into ATMEGA328 microprocessor through a daisy-chained I^2^C connection. The microprocessor will perform sensor fusion which involves the fusion of data to a 4-dimensional quaternion orientation vector using the algorithm devised by Madgwick [20] to denote the orientation of the sensor with respect to gravity. This is followed by date and time stamping the orientation. The resulting date/time-stamped orientation data is transmitted to the iPad using Bluetooth 4.0 connection. The patient application in the iPad will analyze the data to determine the orientation of the two limb sensors. The orientation data in turn is used to calculate the angle of movement as performed by the participant.

